**2 STUDY OVERVIEW AND PROTOCOL SUMMARY**

Study population: Women presenting for routine antenatal care in the second and third trimesters of pregnancy.

Number of Sites: Antenatal clinics at ≥3 sites of varied malaria transmission intensity in Africa; proposed collaborating sites in Burkina Faso, Nigeria, and Uganda. (NB: At present, funds are available to complete the study in two sites, in Burkina Faso and in Uganda; if additional resources permit in the future, the study will also be implemented at the Nigerian site.)

Study Duration: Approximately 12 months from the start of study activities at each site, depending on rates of enrollment.

General objective: To determine whether screening pregnant women for malaria with RDTs may detect placental infection and predict risk of poor birth outcomes due to malaria in areas of varied malaria transmission in Africa.

Specific primary objectives:

1. To compare the results of RDTs, microscopy and PCR performed on peripheral blood from women in the second and third trimesters of pregnancy in malaria-endemic areas of Africa.
2. To determine the positive and negative predictive values of results of RDTs, microscopy and PCR performed on peripheral blood from women in the second and third trimesters of pregnancy, as compared with evidence of placental infection by histological examination after delivery.

Specific secondary objectives:

1. To measure and compare the frequency of pregnancy outcomes (infant birth weights, maternal hemoglobin), prevalence of placental malaria, and risk of symptomatic malaria among women in the study cohort. Participants who test positive by RDT at the time of usual IPTp administration will receive artemisinin-combination treatment (ACT) or quinine; participants who test negative by RDT will receive standard-of-care IPTp with SP.
2. To collect samples for future laboratory analyses related to malaria in pregnancy, including the measurement of the prevalence of molecular markers of antimalarial resistance in the study cohorts.

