## 4.1 General objective

To determine whether screening pregnant women for malaria with RDTs may detect placental infection and predict risk of poor birth outcomes due to malaria in areas of varied malaria transmission in Africa.

Specific primary objectives:

1. To compare the results of RDTs, microscopy and PCR performed on peripheral blood from women in the second and third trimesters of pregnancy in malaria-endemic areas of Africa.
2. To determine the positive and negative predictive values of results of RDTs, microscopy and PCR performed on peripheral blood from women in the second and third trimesters of pregnancy, as compared with evidence of placental infection by histological examination after delivery.

Specific secondary objectives:

1. To measure and compare the frequency of pregnancy outcomes (infant birth weights, maternal hemoglobin), prevalence of placental malaria, and risk of symptomatic malaria among women in the study cohort. Participants who test positive by RDT at the time of usual IPTp administration will receive artemisinin-combination treatment (ACT) or quinine; participants who test negative by RDT will receive standard-of-care IPTp with SP.
2. To collect samples for future laboratory analyses related to malaria in pregnancy, including the measurement of the prevalence of molecular markers of antimalarial resistance in the study cohorts.
3. **STUDY DESIGN**

(See Figure 1 on next page.) Women will be enrolled at their initial presentation for antenatal care after quickening, i.e. on the first antenatal visit when they are eligible for IPTp according to WHO recommendations.2 On the usual IPTp schedule, typically once in the second and once in the third trimester, blood will be collected from all participants for RDT testing, preparation of thick and thin smears for light microscopy, and PCR. RDTs detecting histidine-rich protein 2 (HRP2) and plasmodium lactate dehydrogenase (pLDH) will be used for testing. All participants with negative RDT results will receive SP, and those with a positive RDT result will receive ACT or quinine (according to national policy for treatment of malaria in pregnancy). All participants will be followed up to delivery. At delivery maternal peripheral and placental blood samples will be collected for RDT testing, light microscopy, and PCR, and placental tissue samples will be processed for histopathological examination. Measurement of maternal hemoglobin and infant birth weight will be obtained.

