**7 METHODS AND STUDY PROCEDURES**

**7.1 Study sites and personnel**

*7.1.1 Selection of study sites*

Study sites in each country will be health centers, either government-run or private/missionary, that provide routine antenatal and peri-natal care. The health centers for this evaluation will be selected on the basis of the following characteristics: representation from a range of malaria transmission and geographic zones within Africa; interest and capacity of local researchers and public health authorities; accessibility from the collaborating research team’s base; interest and capacity of the health center staff; and patient numbers adequate to allow enrollment of the target sample size within a period of approximately 6 months. On the basis of current information and preliminary agreements, selected sites include: Colsama government health center in District de Dô, a peri-urban area near Bobo-Dioulasso, Burkina Faso (seasonal transmission); St Kizito Catholic Hospital and/or Regina Mundi Catholic Hospital, Lagos, Nigeria (low year-round transmission); and Tororo District Hospital in eastern Uganda (high year-round transmission). If for unforeseen reasons we are unable to conduct the evaluation at the specific centers listed, alternative sites will be chosen to preserve the representative range of geography and malaria endemicity.

*7.1.2 Personnel conducting protocol activities*

For the purposes of this study, routine antenatal and delivery care will be provided by the staff of participating health centers, i.e. health workers who are employed by the health center (all participating health centers are either government- or missionary-sponsored established health facilities). Such health workers typically include midwives, nurses, and other similar cadres of health care staff. In this protocol, these personnel are referred to as “health center staff.”

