**11.1 Study outcome measures**

Results of peripheral blood tests performed during gestation will be analyzed for associations with evidence of placental malaria and pregnancy outcomes. The statistical analysis will focus on three primary outcomes: 1) negative predictive power of malaria RDTs, peripheral blood films and PCR performed on peripheral blood to diagnose placental malaria during gestation, 2) association of placental malaria during gestation on mean infant birth weight and 3) association of placental malaria during gestation on mean maternal Hb. These outcomes will be used to assess the potential utility of RDTs as screening tests to identify clinically significant malaria infections at a time when effective preventive measures may be taken. Other factors known to influence the study outcomes, including iron and folate supplementation, bed net use and administration of antihelminthic drugs will be treated as confounders in the analysis. In addition, stratified analysis will be conducted to assess these associations within subgroups based on geographic location, estimates of malaria endemicity, participant age, and parity (gravida class).

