**11.3 Sample size considerations**

The target sample size for the number of participants at each study site is calculated to test the hypothesis Ho: [PPV ≤ (disease prevalence + α) or NPV ≤ (1-disease prevalence)] with 80% power and 5% significance at each study location. For the higher transmission sites of Uganda and Burkina Faso α=0.4, while α=0.3 for Nigeria. Previously published estimates of sensitivity (65%) and specificity (98%) were used in these calculations.

Using the target sample sizes outlined below the study will be powered to detect changes in infant birth weight and maternal Hb of >85g and 0.34g/dl, respectively. The sample size for the Burkina Faso site should also allow detection of changes in infant birth weight (>123g) with sufficient power. Based on published data, other sites will not be individually powered to detect likely changes in birth weight (~123g) and none of the sites will be individually powered to detected likely changes in maternal Hb (~0.4g/dl). However this will not prohibit any of the statistical analysis planned.

We estimate that the statistical requirements of the study can be met by enrolling 345 women at the high-transmission Ugandan site, 460 women at the low-transmission Nigerian site, and 860 women at the seasonal-transmission site in Burkina Faso, for a total sample size of 1,665 participants. This estimate assumes a 15% loss to follow-up at each study location.

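### One location per transmission level and an unfunded low-transmission site limit the conclusions to seasonal and high year-round transmission, with no site difference attributable to endemicity

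*Protocol*

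**What the plan says.** Section 2 of the protocol plans "Antenatal clinics at ≥3 sites of varied malaria transmission intensity in Africa". It then states that "At present, funds are available to complete the study in two sites, in Burkina Faso and in Uganda", and that "if additional resources permit in the future, the study will also be implemented at the Nigerian site". The general objective (sections 2 and 4.1) asks whether RDT screening may detect placental infection and "predict risk of poor birth outcomes due to malaria in areas of varied malaria transmission in Africa".

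Section 7.1.1 attaches one transmission label to each country. Burkina Faso is one government health centre in "a peri-urban area near Bobo-Dioulasso, Burkina Faso (seasonal transmission"). The other two are "Lagos, Nigeria (low year-round transmission); and Tororo District Hospital in eastern Uganda (high year-round transmission"). Nigeria may use one or two hospitals, both in Lagos and under the same label.

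Section 11.1 plans stratified analyses "within subgroups based on geographic location, estimates of malaria endemicity, participant age, and parity (gravida class"). The variable table in section 11.2 has study site but no endemicity variable. Section 11.3 sizes each site separately: "For the higher transmission sites of Uganda and Burkina Faso α=0.4, while α=0.3 for Nigeria". The targets are 345 (Uganda), 460 (Nigeria) and 860 (Burkina Faso), in total 1,665.

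**The concern.** Two features combine. First, location and endemicity are listed as separate subgroup factors although the site list gives them the same partition. A reader of the results could take an endemicity table as evidence on transmission when it shows a contrast between countries. Site also carries other differences that the protocol itself builds in: the curative drug follows national policy (sections 5 and 7.3.3), and smears are read at a laboratory belonging to each site (section 7.6.3.1).

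Second, section 2 discloses the funding limit, but nothing later adapts to it. The objective, the total of 1,665, the Nigerian hypothesis with α=0.3 and the pooled detectable differences all still assume three sites.

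At stake is how far the results reach. Primary objective 2 concerns positive and negative predictive values, which depend on prevalence. Section 3.1.1 says malaria in pregnancy takes a different form where transmission is low, section 3.1.4 counts declining transmission among the reasons for new research, and section 13 hopes to inform control policy. Figures from the two funded sites could be carried to a setting that contributed no data.

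**Working it through.** **1. Sample size (section 11.3).** Three sites: 345 + 460 + 860 = 1,665, which reproduces the stated total. Funded sites: 345 + 860 = 1,205. Nigeria's share: 460/1,665 = 27.6%. The low-transmission count falls from 460 to 0.

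**2. Aliasing (sections 7.1.1 and 11.1).** As planned there are three locations and three labels; as funded, two and two. Sites minus levels is 3 − 3 = 0 or 2 − 2 = 0, so there is no replication of sites within a level from which to separate transmission from country. Clinics added under Table 2 in section 16 must lie in the same area, so they would not change this. The replacement rule in section 7.1.1 preserves the endemicity range, but it is tied to unforeseen events, and this shortfall is foreseen.

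**3. Why predictive values do not carry over.** Section 11.3 assumes sensitivity (se) 0.65 and specificity (sp) 0.98. With prevalence p:

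- PPV = se·p / [se·p + (1 − sp)(1 − p)]
- NPV = sp(1 − p) / [sp(1 − p) + (1 − se)p]

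The protocol gives no site prevalences. The 25% below is the one-in-four figure for stable transmission without prevention in section 3.1.1; 10% and 5% are assumptions for illustration.

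| p | PPV | NPV |
|---|---|---|
| 0.25 | 0.1625/0.1775 = 92% | 0.7350/0.8225 = 89% |
| 0.10 | 0.0650/0.0830 = 78% | 0.8820/0.9170 = 96% |
| 0.05 | 0.0325/0.0515 = 63% | 0.9310/0.9485 = 98% |

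**4. Pooled detectable differences.** Section 11.3 states 85 g and 0.34 g/dl for the full target. They cannot be rebuilt, because no SD or RDT-positive share is given, but they can be rescaled. With both held constant, the detectable difference is proportional to 1/√N. The 15% loss is the same at each site and cancels.

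- Factor: √(1,665/1,205) = 1.175
- Birth weight: 85 × 1.175 ≈ 100 g
- Maternal Hb: 0.34 × 1.175 ≈ 0.40 g/dl

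The same scaling agrees with what section 11.3 says about single sites. Burkina Faso alone gives 85 × √(1,665/860) ≈ 118 g, below the likely change of about 123 g, and the section says that site can detect it. Uganda gives 85 × √(1,665/345) ≈ 187 g and Nigeria 85 × √(1,665/460) ≈ 162 g, and the section says they cannot. For Hb, even Burkina Faso gives 0.34 × √(1,665/860) ≈ 0.47 g/dl, above the likely 0.4 g/dl, and the section says no single site is powered for that.

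The per-site targets could not be confirmed or refuted, because they depend on the unstated prevalences.

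**The case against.** The strongest reply is that the plan promises less than the concern suggests. The phrase about varied transmission describes the setting; no test of a transmission effect is stated, and neither primary objective compares levels. Section 11.1 speaks of associations within subgroups, which means estimation inside each stratum. Section 11.2 analyses accuracy separately by location, and section 11.3 sizes each location on its own, so losing Nigeria leaves the predictive-value tests in Uganda and Burkina Faso intact. Section 2 states the funding limit openly, and keeping a Nigerian target in a protocol that may yet open that site is coherent. Endemicity is not defined in section 11.1 and might be measured other than by the site label.

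Most of this stands. A reader might infer that the objective cannot be answered at all. The documents do not support that: seasonal and high year-round transmission are different settings, and section 11.3 itself distinguishes them, although it groups both as higher than Nigeria when setting α. Nor do they support a claim that gravidity mix or calendar period is an uncontrolled difference between sites. Gravidity is a listed confounder and a stratification factor, and no text says the sites run at different times. Shared safeguards also narrow the measurement differences: microscopist qualification, external slide review, one PCR laboratory and a single lot per RDT type.

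What the reply does not remove is that disclosure in section 2 leaves sections 4, 11.1 and 11.3 uncorrected, and that an endemicity stratum built on site labels adds nothing to location while inviting a reading it cannot bear.

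**Conclusion.** The point holds in a limited form. With one location per level, a difference between strata cannot be assigned to transmission intensity. As funded, the study yields no low-transmission evidence, and the α=0.3 hypothesis goes untested unless Nigeria opens. The two primary objectives can still be met for each funded site.

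The numerical effect is 460 fewer women (27.6%) and pooled detectable differences about 17.5% larger. For Hb this matters: about 0.40 g/dl equals the likely change that section 11.3 quotes, so the margin that the pooled analysis had at 0.34 g/dl disappears. These figures assume an unchanged SD and RDT-positive share. If the low-transmission site would have contributed proportionally fewer RDT-positive women, and positives are the smaller group overall, the loss of precision is less, and 100 g and 0.40 g/dl lie towards the unfavourable end. The aliasing result assumes that endemicity is assigned by the labels in section 7.1.1.

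**What to change.** - **Sections 2 and 4:** state that, unless the Nigerian site opens, the objective and conclusions apply to seasonal and high year-round transmission only.
- **Section 11.1:** replace the separate endemicity subgroup with reporting by named site, and state that differences between sites will not be attributed to transmission intensity. The second part matters more; removing a duplicate label alone would change no result.
- **Section 11.3:** state that the α=0.3 hypothesis is untested if Nigeria does not open. Give the two-site total (1,205) and two-site pooled detectable differences beside the three-site figures, recalculated from the sponsor's own SD and RDT-positive share; about 100 g and 0.40 g/dl are the values if neither changes.

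This needs edits to four sections and one short recalculation, with no new data. The price is a narrower stated conclusion and slightly less favourable power figures.

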**3 BACKGROUND AND RATIONALE**

**3.1 Background Information**

*3.1.1 Epidemiology and risks of malaria in pregnancy*

Pregnant women are at particular risk of malaria infection and its consequences. An estimated 50 million women in endemic areas become pregnant each year, and of these approximately half are in sub-Saharan Africa where *Plasmodium falciparum* infections predominate and transmission intensity is significantly higher than in other parts of the world.1, 2 Based on review of cross-sectional data, in the absence of preventive efforts it is estimated that approximately one in four pregnant women in areas of stable malaria transmission in Africa have evidence of infection at the time of delivery.3 In moderate and high transmission areas, younger women and paucigravidae are typically at higher risk than older women and multigravidae, indicating some protective effect of age- and parity-specific immunity.4-6 The risks presented to mother and fetus by malaria infection may be exacerbated by co-existing conditions including malnutrition, other parasitic infections, and HIV infection.1, 7

The negative effects of malaria infection in pregnancy have been recognized for decades.8-11 The specific effects of malaria in pregnancy depend on host immunity, which depends in turn on malaria transmission intensity.2 In areas where malaria transmission is low or unstable, individuals do not acquire immunity with repeated exposure, and pregnant women typically develop symptoms when parasitemic. In these epidemiologic conditions, important risks of malaria in pregnancy include spontaneous abortion, premature delivery, stillbirths, and maternal death from severe malaria. In contrast, in areas where malaria transmission is moderate to high and stable, adults develop partial immunity through repeated exposure, and most malaria infections are asymptomatic. Under these conditions, pregnant women are at risk for anemia (including severe anemia with potential for maternal death)12 and placental malaria. Placental malaria infection, while often asymptomatic, has been clearly shown to be associated with low birth weight due to both premature delivery and intrauterine growth retardation; low birth weight in turn is associated with higher rates of infant mortality and poor child development.1, 2, 13, 14

*3.1.2 Diagnosis of malaria in pregnancy*

For purposes of epidemiological investigations, the gold standard for diagnosis of malaria in pregnancy is histopathological examination of the placenta after delivery.15-17 As recently summarized by Rogerson, et al, microscopic observation of histological changes in the placenta, including the presence of hemozoin deposits, may be used to confirm current and previous malaria infections, and a variety of laboratory protocols have been suggested for preparation of such samples.16, 18 A number of studies have documented the low sensitivity of light microscopy of peripheral blood smears for detecting placental infection.19 Importantly, some studies have indicated that submicroscopic malaria infections, identified with PCR or antigen-detection tests, may be associated with negative clinical outcomes including maternal anemia19, 20 and low birth weight.21 However, PCR is not available outside research settings, and antigen-detection tests have not yet been evaluated adequately for use in pregnancy.

Rapid diagnostic tests (RDTs) detect parasite antigen circulating in the blood of infected individuals. Malaria RDTs, which do not require the laboratory infrastructure or expertise of microscopy, are increasingly seen as a reliable alternative for symptomatic case management in virtually all endemic settings. The accuracy of well-made and correctly performed RDTs has been demonstrated in a variety of settings.22-25 The WHO currently recommends that parasite-based diagnosis, with either microscopy or rapid diagnostic tests (RDTs), be used for case management in all malaria-endemic areas except in certain circumstances (e.g. severe outbreaks proven to be malaria in resource-poor situations, young children in high transmission settings).26 Many malaria control programs in Africa are working to institute national policies of parasite-based diagnosis, and to expand availability of parasite-based diagnosis to more remote areas through the use of RDTs. The quality of commercially produced RDTs is formally evaluated by product testing and lot-testing through the WHO/FIND malaria RDT evaluation program in collaboration with the US Centers for Disease Control and Prevention and a network of other laboratories (<http://www.wpro.who.int/sites/rdt/who_rdt_evaluation/>).27 In addition, the WHO/FIND program facilitates lot testing of RDTs procured by national malaria control programs through a network of regional laboratories (<http://www.wpro.who.int/sites/rdt/who_rdt_evaluation/lot_testing.htm>).

We have identified seven publications on six studies that evaluated RDTs for detection of malaria infections in peripheral and/or placental blood at delivery.19, 28-32 In general, these studies show that at delivery, the correlation of RDT results (and especially histidine-rich protein 2 [HRP2] RDT results) in peripheral blood with evidence of placental infection falls somewhere between that of microscopy and PCR. However, none of the published studies compared birth outcomes or placental findings with testing performed during gestation (as opposed to at delivery), and none reported results of placental histology. More recently, a study in southwest Uganda monitored pregnant women weekly with microscopy, HRP2-based RDT and PCR, and found an RDT sensitivity of 65% and specificity of 99% when compared with PCR on the same peripheral blood sample.[[name], personal communication] Another recently-completed study from Ghana compared three treatment groups: one group of pregnant women received IPTp with SP, the second received SP only if the screening RDT was positive, and the third group received artesunate+amodiaquine if the screening RDT was positive. Preliminary results from this study show no statistically significant difference among the groups in severe maternal anemia or risk of low birth weight.[[name], personal communication] In summary, as yet there is no confirmed sensitive and practical approach to diagnosing placental malaria during gestation, at a time that more efficacious preventive measures could be appropriately targeted; but evidence to date on the potential for RDTs to fill this role is promising.

*3.1.3 Current prevention and control methods for malaria in pregnancy*

In light of the heavy burden of malaria in pregnancy, and the lack of practical diagnostic strategies and facilities, the WHO’s strategic framework for prevention and control of malaria in areas of stable transmission – which includes much of sub-Saharan Africa – includes intermittent preventive treatment in pregnancy (IPTp), insecticide-treated bed nets (ITNs), and case management of malaria illness and anemia.2 For treatment of symptomatic malaria illness in the second and third trimesters of pregnancy in Africa, the WHO currently recommends artemisinin-based combination treatment (ACT) on the basis of significant evidence of efficacy and safety.26, 33 For prevention, the WHO recommends: “In areas of high transmission, IPT with SP should be administered to pregnant women at least twice during the second and third trimesters of pregnancy, and three times in the case of HIV-positive pregnant women. The effectiveness of IPT should be monitored in light of increasing SP resistance.”34 By the end of 2006, 33 of the 45 African countries had adopted IPTp as national policy.34 The evidence base for benefit of IPTp with SP is broad, supported by a number of studies conducted in the 1990s and early 2000s.35-39 Specifically, the intervention has been clearly shown to significantly reduce the prevalence of maternal anemia, the prevalence of placental parasitemia, and the incidence of low birth weight. However, reduced parasite susceptibility to SP appears to threaten the effectiveness of IPTp with this drug.

*3.1.4 Potential loss of efficacy of IPTp with SP due to parasite resistance*

Over the past several years, the spread of resistance to SP as a regimen for treatment of symptomatic malaria infections has been widely recognized. Mutations in the parasite genes for dihydropteroate synthase (DHPS) and dihydrofolate reductase (DHFR) mediate resistance to sulfadoxine and pyrimethamine, respectively, and parasites with multiple mutations in both genes are common throughout East and Southern Africa,40 including in study populations of pregnant women,41 and appear to correlate negatively with treatment outcomes especially in individuals with less acquired immunity.42, 43 A 2007 review paper reported continued benefit of IPTp with SP in areas with high rates of SP treatment failure;44 however, a recent study in Tanzania identified a new “triple: triple” mutant parasite and documented associated high failure rates of SP in treatment of symptomatic children and asymptomatic infants,45 and data on decreasing effectiveness of IPTp with SP is beginning to emerge.[[name], unpublished data]

Because of evidence of increasing SP resistance, and potential implications for loss of efficacy of IPTp with SP, as well as evidence for declining malaria transmission rates in many parts of Africa and a consequent need to rethink the risk/benefit ratios of preventive methods, the WHO and others have called for research into new approaches to prevention of malaria in pregnancy.2, 46-48

